## Abstract

**Background:**

Antiplatelet treatment is an important component in optimizing the clinical outcomes after percutaneous coronary intervention (PCI) especially in patients with acute coronary syndrome (ACS). Prasugrel, which is a new P2Y12 inhibitor, has been confirmed as efficacious in a large trial in Western countries, and a similar trial is also to be launched in Asian countries. Although a 60-mg loading dose of prasugrel followed by 10 mg per day should be acceptable, there have been no data regarding the optimal dose in Asian patients. Furthermore, serum levels of prasugrel and the rates of platelet inhibition are known to be higher in Asians than Caucasians with the same dose of the drug.

Polymer, a key component of drug-eluting stents (DES), has been suggested as the cause of inflammation leading to late complications, and has driven many companies to develop biodegradable-polymer DES. Currently, there are limited data regarding the head-to-head comparison between BP-BES and the biostable polymer CoCr-EES or the newest platinum-chromium everolimus-eluting stent (PtCr-EES). Furthermore, the polymer issue may be more important in ACS where there is ruptured thrombotic plaque where polymer-induced inflammation may affect the local milieu of the stented artery.

Therefore, the present study dedicated only to ACS patients, will offer important information on the optimal prasugrel dose in the Asian population by comparing a 10-mg versus a 5-mg maintenance dose beyond 1 month after PCI, as well as giving important insight into the polymer issue by comparing BP-BES versus biostable-polymer PtCr-EES.

**Method/Design:**

Harmonizing Optimal Strategy for Treatment of coronary artery diseases – comparison of REDUCtion of prasugrEl dose or POLYmer TECHnology in ACS patients (HOST-REDUCE-POLYTECH-ACS) trial is a multicenter, randomized and open-label clinical study with a 2 × 2 factorial design, according to the type of stent (PtCr-EES versus BP-BES) and prasugrel maintenance dose (5 mg versus 10 mg), to demonstrate non-inferiority of PtCr-EES relative to BP-BES or the reduced prasugrel dose relative to conventional dose in an Asian all-comers PCI population presenting with ACS. Approximately 3400 patients will undergo prospective, random assignment separately to either stent or prasugrel arm (1:1 ratio, respectively). When the patients have contraindications to prasugrel, they are categorized into an antiplatelet observation group after stent-randomization. The primary endpoint is the patient-oriented composite outcome, which is a composite of all-cause mortality, any myocardial infarction (MI), any repeat revascularization in the stent arm at 12 months after index PCI. In the prasugrel arm, primary endpoint is any major adverse cardiovascular event, which is a composite of all-cause mortality, any MI, any stent thrombosis (Academic Research Consortium (ARC)-defined), any repeat revascularization, stroke, or bleeding (BARC class ≥ 2).

**Discussion:**

The HOST-REDUCE-POLYTECH-ACS RCT is the first study exploring the optimal maintenance dose of prasugrel beyond 1 month after PCI for ACS in Asian all-comers. In addition, this is the largest study dedicated only to ACS patients to evaluate the polymer issue in the situation of ACS by directly comparing biostable-polymer PtCr-EES versus BP-BES.

**Trial registration:**

ClinicalTrials.gov (ID: NCT02193971, 13 July 2014).

## Background

Acute coronary syndrome (ACS) is a leading cause of death and hospitalization in developed countries. In recent decades, the mortality and morbidities after ACS have been remarkably decreased with improvement in percutaneous coronary intervention (PCI) with a drug-eluting stent (DES) and treatment with antiplatelet agents [1, 2].

Prasugrel is a novel thienopyridine that irreversibly binds to the platelet P2Y12 receptor and inhibits adenosine diphosphate-induced platelet aggregation. Both agents are thienopyridine P2Y12 inhibitors, but prasugrel is more potent and has less variability in platelet inhibition than clopidogrel. In the TRITON-TIMI 38 trial enrolling ACS patients with planned PCI (mostly after diagnostic angiography), prasugrel significantly reduced ischemic events including stent thrombosis (ST) but increased major bleeding episodes, including fatal ones, compared with clopidogrel [3]. Currently, guidelines recommend prasugrel as an initial P2Y12 inhibitor over clopidogrel, unless the patients are older than 75 years of age, have low body weight (<60 kg), or previous history of transient ischemic attack or stroke [4]. Nonetheless, clinical efficacy and safety of prasugrel in Asians are still unclear. Studies have shown marked inter-ethnic difference in the pharmacokinetics and pharmacodynamics of prasugrel. Asians showed higher serum prasugrel levels with greater platelet inhibition than Caucasians at the same dose of prasugrel [5]. In terms of balance between bleeding and thrombosis, Asians have a lower risk of thrombotic event while a higher risk of bleeding in previous studies [6]. In addition, East Asians have not been properly enrolled in major clinical trials with prasugrel (7.8 % in TRIOLGY ACS, and 0.9 % in TRITON-TIMI 38) [3, 7]. In this regard, concerns need to be addressed in a dedicated trial of East Asians as to whether the currently recommended dose of prasugrel (60 mg loading/10 mg daily maintenance) is efficacious and also safe in East Asians.

In this study, we will compare 2 different maintenance doses of prasugrel beyond 1 month after PCI: conventional dose of 10 mg versus a reduced dose of 5 mg of prasugrel in Asian patients with ACS undergoing PCI. All of the enrolled patients will receive the currently recommended loading dose of prasugrel (60 mg), and maintain a 10-mg daily dose for the first month. After 1-month clinical follow-up, patients will receive maintenance dosage randomly assigned after PCI (10 mg versus 5 mg). Dual antiplatelet therapy is recommended for at least 1 year. Clinical adverse events, including bleeding, will be compared at 1-year clinical follow-up.

Another important issue is the efficacy and safety of DES in treating unstable coronary plaques of ACS patients. There had been a concern that DES may increase the risk of late or very late ST, and that DES use in treating unstable vulnerable plaques may lead to worse outcomes. However, many trials including the HORIZONS-AMI and the ACUITY trial have already confirmed efficacy and safety of DES even in ACS patients [8, 9]. Technological innovations have led to the development of second-generation DES with a thinner strut with biocompatible polymer, or third-generation DES with biodegradable-polymer. One of the representatives of second-generation DES with a biocompatible polymer is cobalt-chromium-based everolimus-eluting stent with fluorinated co-polymer coating (CoCr-EES). The CoCr-EES has shown to reduce repeat revascularization and ST in patients with ST elevation myocardial infarction (MI) compared to bare metal stents (BMS) [10]. Also, CoCr-EES (Xience V®, Promus®, Xience Prime®, Xience Xpedition®, Abbott Vascular, CA, Illinois, USA) has proved its excellent safety and efficacy in diverse populations with numerous registries, trials and network meta-analyses [11–15]. Otherwise, the biodegradable polymer-coated biolimus-eluting stent (BP-BES, Biomatrix®, Biomatrix Flex® and Nobori®, Biosensors, Newport Beach, CA, USA, and Terumo Corporation, Tokyo, Japan) adopted the polymer poly-D-L-lactic acid (PDLLA) which is fully metabolized within 6–9 months in the human body. It was developed with the aim of eliminating the inflammatory stimulus and to thereby reduce the risk of ST. BP-BES in reality has shown excellent safety in long-term outcomes. In the LEADERS trial, BP-BES showed a significantly lower rate of very late ST (>1 year) than the durable-polymer sirolimus-eluting Cypher stent [16]. Even in comparison with BMS, BP-BES showed better efficacy and a trend toward better safety in a dedicated trial for patients with ST-segment elevation MI (STEMI), COMFORTABLE AMI [17]. In network meta-analyses, however, BP-BES was consistently inferior to CoCr-EES in terms of safety [14, 15, 18]. The results of meta-analyses look somewhat different from the recent data of individual trials comparing CoCr-EES and BP-BES: for example, the NEXT trial or COMPARE II trial, which both showed comparable safety and efficacy between the two stents [19, 20]. This discrepancy might originate mostly from heterogeneity in the BP-BES group having 17 different BP-DES in the meta-analyses [21]. Currently, there are limited data regarding the head-to-head comparison between BP-BES and CoCr-EES or platinum-chromium-based everolimus-eluting stent (PtCr-EES). Therefore, we need more evidence to clarify whether polymer technology is important and influences clinical outcome. The polymer issue may be more important in ACS patients who have ruptured plaques and a coronary artery thrombosis where polymer may affect the microenvironment of the stented artery. In terms of metal, platinum-chromium alloy is the newest metal in the stent industry, is known as a very inert alloy, and may result in less vessel injury and inflammation after PCI.

Therefore, this randomized trial dedicated only to ACS patients, with a 2 × 2 factorial design will address: (1) whether the reduced (5 mg) maintenance dose of prasugrel is non-inferior to regular (10 mg) dose in maintenance period beyond 1 month after PCI for ACS, and (2) whether a newly-developed biostable polymer PtCr-EES (Promus Premier^TM^, Boston Scientific, Natick, MA, USA) is at least non-inferior to BP-BES (Biomatrix®, Biomatrix Flex®, or Nobori®, Biosensors, Newport Beach, CA, USA, and Terumo Corporation, Tokyo, Japan) in preventing target lesion failure in ACS patients.

## Methods

### Study objectives and hypotheses

The primary objectives of this study, with a 2 × 2 factorial design are: (1) to evaluate the safety and efficacy of 2 different maintenance doses of prasugrel beyond 1 month after PCI: the reduced maintenance dose of prasugrel (5 mg daily) versus conventional dose of prasugrel (10 mg) in ACS patients, and (2) to determine the safety and long-term efficacy of coronary stents with 2 different polymer technologies: biostable polymer PtCr-EES versus BP-BES. The working hypotheses of this study are: (1) that a reduced dose of prasugrel (5 mg daily) is non-inferior to a conventional dose (10 mg daily) in preventing major adverse cardiovascular events (MACE) at 12 months, and (2) that PtCr-EES is non-inferior to BP-BES in reducing patient-oriented composite outcome (POCO), defined as a composite of all-cause death, nonfatal MI, and any repeat revascularization at 12 months. MACE is defined as a composite of all-cause death, nonfatal MI, ST, repeat revascularization, cerebrovascular accident (CVA), and Bleeding Academic Research Consortium (BARC) class ≥ 2 bleeding [22].

### Study design

This is a prospective, open-label, multicenter, randomized controlled trial with a 2 × 2 factorial design. The flow chart of patients is shown in Fig. 1. The 27 cardiovascular centers in Korea will participate in this trial. Clinical follow-up will occur at 1, 12, 24, 36 months after index procedure. Investigators may conduct this follow-up as telephone interviews or office visits. There will be no mandatory angiographic follow-up unless clinically necessary. Prasugrel on-treatment platelet reactivity will be measured by using VerifyNow P2Y12 assay (Accumetrics, San Diego, CA, USA) in the antiplatelet arm at index procedure and at 1-month, and 12-month follow-up for the pre-specified subgroup analysis.

**Fig. 1 Fig1:**
[figure not shown]
HOST-REDUCE-POLYTECH-ACS trial algorithm. *Abbreviations*: *ACS* acute coronary syndrome, *BP*-*BES* biodegradable polymer-coated biolimus-eluting stent, *PCI* percutaneous coronary intervention, *PtCr*-*EES* platinum-chromium-based everolimus-eluting stent, *TIA* transient ischemic attack

This trial is investigator-initiated, with grant support from Boston Scientific Korea, DIO co., and TERUMO Korea. Other than financial sponsorship, the companies have no role in protocol development or the implementation, management, data collection, and analysis of this study. The authors alone are responsible for design and execution of the trial, related statistical analyses, and all aspects of manuscript preparation, including drafting, editing, and final content. This study will be conducted according to principles outlined in the Declaration of Helsinki. All patients must provide written informed consent. This study protocol has been approved by the institutional review board of 22 participating centers in Korea. The study protocol was registered at www.clinicaltrials.gov (NCT02193971, https://clinicaltrials.gov/ct2/show/NCT02193971).

### Study population and entry criteria

ACS patients with at least 18 years of age who meet all of the inclusion criteria (Table 1) are eligible for this study. Patients must have a culprit lesion in a native coronary artery or a graft vessel with significant stenosis (>50 % by visual estimate) eligible for stent implantation as in the current recommendations of ACC/AHA/SCAI and ESC/EACTS guidelines [4, 23]. Patients with known hypersensitivity or contraindication to heparin, aspirin, clopidogrel, prasugrel, ticagrelor, biolimus, everolimus, or contrast media will be excluded. Additional exclusion criteria will be systemic (intravenous) biolimus, or everolimus use within 12 months, with active pathologic bleeding, with gastrointestinal or genitourinary bleeding within the prior 3 months, women of childbearing potential, history of bleeding diathesis, known coagulopathy (including heparin-induced thrombocytopenia), or refused blood transfusions, presence of non-cardiac co-morbid conditions with life expectancy less than 1 year or conditions that may result in protocol non-compliance. Inclusion and exclusion criteria will be graded to minimize exclusion of patients, thus reflecting a population at-large.

**Table 1 Tab1:** Enrollment criteria

General inclusion criteria
1. Subject must be ≥ 18 years
2. Subject is able to verbally confirm understandings of risks, benefits and treatment alternatives of receiving percutaneous coronary intervention and he/she or his/her legally authorized representative provides written informed consent prior to any study related procedure
3. Subject must have a culprit lesion in a native coronary artery with significant stenosis (>50 % by visual estimate) eligible for stent implantation
4. Subject must have clinical diagnosis of acute coronary syndrome that includes unstable angina (crescendo, new-onset, resting) and myocardial infarction
Exclusion criteria
● The following patients will be enrolled in stent comparison, but excluded from antiplatelet prasugrel comparison. They will be classified as antiplatelet observational cohort:
1. Subjects ≥ 75 years
2. Body weight < 60 kg
3. History of TIA or stroke
1. The patient has a known hypersensitivity or contraindication to any of the following medications: heparin, aspirin, clopidogrel, prasugrel, ticagrelor, biolimus, everolimus, contrast media (patients with documented sensitivity to contrast media (e.g. rash) who can be effectively premedicated with steroids and diphenhydramine] may be enrolled. Those with true anaphylaxis to prior contrast media, however, should not be enrolled)
2. Patients with active pathologic bleeding
3. Gastrointestinal or genitourinary bleeding within the prior 3 months, or major surgery within 2 months
4. Systemic (intravenous) biolimus, or everolimus use within 12 months
5. Woman of childbearing potential, unless a recent pregnancy test is negative, who possibly plans to become pregnant any time after enrollment into this study
6. History of bleeding diathesis, known coagulopathy (including heparin-induced thrombocytopenia), or will refuse blood transfusions
7. Non-cardiac co-morbid conditions are present with life expectancy < 1 year or that may result in protocol non-compliance (per site investigator’s medical judgment)

*TIA* transient ischemic attack

If all eligible criteria are met and written informed consent is provided, patients will be randomized 1:1 to either (a) PtCr-EES or (b) BP-BES group, and 1:1 to either (a) reduced dose of prasugrel (5 mg daily) or (b) the conventional dose (10 mg daily) group. Patients who meet the exclusion criteria of prasugrel (age ≥ 75 years, body weight < 60 kg, or history of transient ischemic attack or stroke) will be enrolled in stent comparison, but excluded from prasugrel comparison. To generate comparable groups relative to known and unknown risk factors, randomization will be independently conducted online (T&W Software, Seoul, Korea) via web-based application. All randomization will be balanced, stratified by participating center and allocated treatment groups. According to the consideration of calculated sample size to meet non-inferiority in each comparison arms, a total of 3384 patients from 22 centers in Korea will be planned to be enrolled.

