### Statistical considerations

#### Sample size calculations

Based on the event rates of a previous all-comer trial performed with the Korean population, we predicted POCO rates of PtCr-EES and BP-BES to be 6 % and 6 % at 12 months after index PCI, respectively [11, 13, 28]. Using a non-inferiority log-rank design with a non-inferiority margin of 2 %, sampling ratio of PtCr-EES:BP-BES at 1:1, allowing 5 % withdrawal rate in each group for the 12 months, a total of 3384 patients would result in a power of at least 81 % power with a 1-sided α of 2.5 %. The expected number of events in the stent comparison arm will be 362 as a total.

Also, to demonstrate the second hypothesis that the reduced dose of prasugrel is non-inferior to the conventional group regarding MACE rates at 12 months, we assumed the MACE rates of the reduced dose group and the conventional dose group to be 7 % and 8 %, respectively [29]. Using a non-inferiority design, a non-inferiority margin of 2.5 %, a sampling ratio of reduced dose group:conventional dose group at 1:1, allowing 5 % withdrawal rate in each group for 12 months, we need total 2348 patients in a statistical power of 75 % with a 1-sided α of 2.5 %. The expected number of events in the antiplatelet comparison arm will be a total of 342.

We expect 30 % of ACS patients’ criteria (age ≥ 75 years, body weight < 60 kg, or history of transient ischemic attack or stroke) would be excluded in the prasugrel comparison, which results in a sample size of 2369. If the number of exclusion criteria in the prasugrel comparison exceeds our expected number, patient recruitment will be done until the number of patients in the prasugrel arm is 2348.

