#### Statistical analyses

All primary and secondary endpoints and serious adverse events will be analyzed after adjudication by a member of researchers or clinicians. All primary and secondary endpoints will be analyzed both on an intention-to-treat basis (all patients analyzed as part of their assigned treatment group), and per-protocol basis. For patients receiving multi-vessel PCI, the target lesion/vessel will be declared by the operator prior to the interventional procedure.

Primary endpoints will be analyzed firstly on an intention-to-treat basis (all patients analyzed as part of their assigned treatment group), and then, on a per-protocol basis at 12 months and 3 years after index procedure. The null hypothesis will be evaluated on a non-inferiority basis with Kaplan-Meier survival with the log rank test. Non-inferiority is defined by a 1-sided alpha of 2.5 % and a difference in net POCO rates of less than 2 % in the stent comparison arm and MACE rate of less than 2.5 % in the antiplatelet comparison arm. All primary and secondary endpoints will be analyzed on a per-patient basis. Events within the first month, the period receiving a 10-mg dose of prasugrel before taking the allocated prasugrel dose, will also be analyzed on an intention-to-treat basis. In addition, a landmark analysis will be performed at 1 month after index PCI, as a sensitivity analysis.

Device-oriented composite endpoint (target lesion failure: a composite of cardiac death, target-vessel MI, or target lesion revascularization) will be analyzed using the *χ*^2^-test and Kaplan-Meier survival with the log rank test. Other secondary endpoints including all-cause and cardiac death, target vessel/lesion revascularization, non-target vessel/lesion revascularization, any revascularization, target-vessel and all-cause (including non-target vessel) nonfatal MI, ST, stroke (ischemic or hemorrhagic), bleeding (BARC classification ≥ 2) will be analyzed using the *χ*^2^-test and Kaplan-Meier survival with the log rank test. Acute procedure success (device, lesion, and procedure) and adherence to study dose of drug (prasugrel) will be analyzed using the *χ*^2^-test. The baseline coronary angiographic characteristics will be analyzed on a per-lesion basis.

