#### Treatment of missing values

The primary analysis of the study endpoints will not be covariate-adjusted. No imputation methods will be used to infer missing values of baseline variables. For the study endpoints, patients lost to follow-up and subsequently lost to assessment of primary endpoint, will be considered to be censored in the estimation of Kaplan-Meier event rates. As a secondary analysis, we will also examine the patients who have been lost to follow-up. We will perform a comparison of baseline characteristics in patients with versus patients without 1-year follow-up. In addition, a sensitivity analysis will be performed to assess the impact of these patients on the study outcomes.

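### Randomization is stratified, but the primary analyses as written leave the stratification factors out: a small, conservative loss of precision

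*Protocol article*

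**What the plan says.** Under Study population and entry criteria, the protocol article states: "All randomization will be balanced, stratified by participating center and allocated treatment groups". It does not explain the second factor. It could mean the arm of the other comparison, or membership of the randomized versus the observational antiplatelet cohort.

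Under Statistical analyses: "The null hypothesis will be evaluated on a non-inferiority basis with Kaplan-Meier survival with the log rank test". No strata, center term or term for the other factor is named. The decision rule is on the scale of a rate difference: "Non-inferiority is defined by a 1-sided alpha of 2.5 % and a difference in net POCO rates of less than 2" % for the stents, and below 2.5 % for the MACE rate in the dose comparison.

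Under Treatment of missing values: "The primary analysis of the study endpoints will not be covariate-adjusted".

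Under Sample size calculations, each comparison is sized by itself as a plain two-group design. About 30 % of patients are expected to be outside the dose comparison while remaining in the stent comparison.

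**The concern.** When allocation is balanced within strata that predict outcome, the between-stratum part of the outcome variation cancels from the treatment difference. A variance formula that ignores the strata still counts it, so the standard error comes out too large.

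Two features of this trial bear on that. The stent comparison pools patients on either prasugrel dose with a cohort aged 75 or over, under 60 kg, or with prior TIA or stroke, who receive other P2Y12 inhibitors and may be at higher risk. The dose comparison has no term for stent. Precision matters here because the Limitations section concedes 75 % power for the dose comparison and little scope to raise it. At stake is some precision in two non-inferiority comparisons, and agreement between design and analysis.

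**Working it through.** **1. The plan's own figures.** Inputs from Sample size calculations: "we predicted POCO rates of PtCr-EES and BP-BES to be 6 % and 6 % at 12 months after index PCI", a margin of 2 %, "sampling ratio of PtCr-EES:BP-BES at 1:1", "allowing 5 % withdrawal rate in each group for the 12 months", and "a total of 3384 patients would result in a power of at least 81 % power with a 1-sided α of 2.5" %, with 362 events.
- Hazard ratio at the margin: ln(0.92)/ln(0.94) = 1.348.
- Schoenfeld power: Φ(ln(1.348) × √362/2 − 1.960) = Φ(0.878) = 81.0 %, as stated.
- Dose comparison, 342 events, with equal true rates of 8 % and margin 2.5 %: hazard ratio ln(0.895)/ln(0.92) = 1.330; power Φ(0.680) = 75.2 %, as stated. The match needs equal rates, not the 7 % versus 8 % written in the article.

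Both figures come from the ordinary unstratified formula.

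**2. Effect of ignoring center and the other factor.** The article gives no between-center variation, so a range was assumed: standard deviation of the center effect on the logit scale from 0 to 0.8, and an odds ratio for the other factor of 1.0 to 1.3 (1.3 in the dose comparison). The simulation used 22 unequal centers, exact balance within center by other factor, a test of the 12-month risk difference, and 20,000 runs per scenario.

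| Comparison | Center SD | Power, unstratified | Power, stratified |
|---|---|---|---|
| Stent, 6 % vs 6 % | 0 | 69.1 % | 69.1 % |
| Stent | 0.5 | 69.3 % | 69.8 % |
| Stent | 0.8 | 69.7 % | 71.0 % |
| Dose, 8 % vs 8 % | 0 | 60.2 % | 60.2 % |
| Dose | 0.8 | 61.7 % | 63.4 % |

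- One-sided type I error over all scenarios: 2.3 to 2.6 % unstratified, 2.4 to 2.7 % stratified. The 2.7 % belongs to the scenario with the largest gain (dose, SD 0.8), so 1.7 points is, if anything, generous.
- Ratio of mean standard errors at SD 0.8: stent 0.00810/0.00795 = 1.019; dose 0.01113/0.01087 = 1.024.
- On the interval for the stents: 1.96 × (0.00810 − 0.00795) = 0.03 percentage points, against a margin of 2.

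The power levels lie below 81 % and 75 % because the test uses 12-month events only (3384 × 6 % = 203, against 362 stated). That is a separate matter, which stratification would not repair.

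**3. Effect of the observational cohort.** The article gives no risk for it, so assume k times the risk of the others, with k from 1.5 to 3. With 30 % in the cohort and 6 % overall, b = 0.06/(0.7 + 0.3k). The within-stratum variance is 0.7·b(1−b) + 0.3·kb(1−kb), against 0.06 × 0.94 = 0.0564.
- k = 1.5: ratio 0.997
- k = 2: ratio 0.992
- k = 3: ratio 0.979

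The variance falls by 0.3 to 2.1 %. At most this is 1 − √0.979 = 1.05 % of the standard error.

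**4. How finely one can stratify.** Center by three antiplatelet groups (5 mg, 10 mg, observational) gives 22 × 3 = 66 strata. That is 3384/66 ≈ 51 patients per stratum, about 26 per arm, and 203/132 ≈ 1.5 events per arm. An average stratum-arm has no event with probability 0.94^26 ≈ 20 %. Its estimated Kaplan-Meier variance is then zero, and inverse-variance weights become unstable or undefined.

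**The case against.** The strongest case against has four parts.

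- *That the test is unstratified is partly inferred from silence.* A statement against covariate adjustment does not strictly exclude a stratified log-rank test, and the analysis plan, which is not shown, may name strata. This stands as a caution. Still, the refusal to adjust is a positive statement, and someone working from the two sections together would run the unstratified analysis.
- *Nothing invalid is done.* This stands. Ignoring balanced strata is conservative, and analysis at the margins is usual and valid for a 2 × 2 design. A reader might infer that each main effect must be estimated within levels of the other factor; that is good practice, not a condition of validity.
- *The observational cohort is not a safe stratum.* The Abstract places these patients in that group after stent randomization. The Limitations section adds relative contraindications and other clinical circumstances to the three fixed criteria. In an open-label trial, membership could therefore depend on what happened after stent allocation, and conditioning on it could bias a comparison that is otherwise unbiased. This stands and limits the fix.
- *Stratifying is not free if done finely.* This stands against inverse-variance weighting over some 66 cells. It does not stand against methods that tolerate sparse strata.

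**Conclusion.** The point holds as a minor misalignment between design and analysis. As written, the randomization factors are left out of both primary analyses. The standard error is then too large by about 2 % at most (2.4 % in the most extreme scenario), and 0 to about 1.7 power points are lost. The upper ends require a center standard deviation of 0.8 on the logit scale, which is an assumption. The contribution of the observational cohort rests on an assumed 1.5- to 3-fold risk.

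A reader might infer that the mismatch undermines a positive non-inferiority finding. It does not: the simulated type I error of the unstratified test stays at 2.3 to 2.6 %, and the effect is conservative. No stated sample size, event count or power has to change because of it. The reason to act is that the correction needs no further patients.

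**What to change.** Amend Statistical analyses and the sentence on covariate adjustment in Treatment of missing values as follows.

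- The primary non-inferiority test and confidence interval account for the randomization factors by a stratified log-rank test or a Mantel-Haenszel-weighted difference in 12-month Kaplan-Meier rates, not by inverse-variance weighting. The weighted difference fits the margins directly, since they are differences in rates.
- Dose comparison: center and allocated stent.
- Stent comparison: center and, if wanted, prasugrel eligibility defined only by the baseline criteria (age 75 or over, weight under 60 kg, prior TIA or stroke). Do not use a classification made after stent allocation.
- Small centers are pooled by a rule set in advance.
- Say in Study population and entry criteria what the allocated treatment groups mean as a stratification factor.
- Keep the unadjusted analysis as a sensitivity analysis.

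The cost is wording, a pooling rule and slightly more analysis work.
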